# Investigational plan

## General Scheme of Study Design and Study Plan:

Quasi-experiment (pre-post design) will be adopted.

The plan is to adopt a four- phased strategy using mixed-method approach, each addressing specific research question (Figure-1).

**Figure-1: Phase-wise research strategy, objectives and activities planned for each phase of the study.**

### Phase-I (Formative research):

Mixed-method design will be adopted.

Phase-I will involve the scoping review to assess the knowledge, attitude and practice (KAP) gap from the literature in LMIC setting. After scoping review, we will conduct a mixed-method analysis in the form of a sequential exploratory design, cross-sectional analysis of administrative data (QUAN) followed by IDIs of surgeons (QUAL).

The quantitative analysis involves the baseline data collection on the burden of SSI and evaluation for surgical practices among healthcare professionals using a cross-sectional analysis (quantitative part). The risk factors which might contribute to the increased risk of SSI will be identified in the settings involved in the study. The qualitative practice assessment form will be formulated using the semi-structured questionnaire to be filled by the surgeons on what practice they follow for various type of surgeries (elective and emergency surgeries) in their setting and if there are any challenges in adoption of the already published guidelines (global guidelines for prevention of surgical site infections by WHO^2^, second edition 2018 and Clinical practice guidelines for antimicrobial prophylaxis in surgery^5^). A semi-structured format allows us to remain open to exploratory findings during the course of interviews.

The qualitative component of this phase of analysis involves In-depth interviews (IDI) with the surgeons will be conducted to explore their perspectives and perceived barriers on implementation of SSI prevention strategies in their respective settings. The number of IDIs will range from 10-15 or until saturation of data is achieved. In addition, the IDI will be conducted with nurses to understand what surgical pre-operative, operative and post-operative measures they follow in routine surgeries in operation theatre and what are the challenges in adoption of already published surgical site infection prevention guidelines as mentioned above?

The baseline data collection will be done by the trained research associate/ICN nurse for the patients undergoing surgeries as per inclusion/exclusion criteria and the baseline SSI rate in the setting will be calculated from the baseline data collected. The baseline data collection will be done using the standard case record form (CRF) designed for the study which will include collection of data on (but not limited to) parameters like type of surgery, American Society of Anesthesiologists (ASA) physical status score (refer to Annexure-V), timing and antimicrobial agent for surgical prophylaxis, duration of surgery, need for redosing of antimicrobial prophylaxis, and other defined parameters. In addition, the observation of practices of the care delivery team and observation of interactions among care team and patients will be done at this stage. This qualitative assessment will allow the research team to observe points that practitioners may not have reflected on or recollect during interviews. The baseline data collection phase will last for 6 months. No intervention or practice change will be applied in this phase.

**Outcome of Phase-I:** Expected outcome of Phase-I will be to identify the knowledge gaps in the practice, barriers and challenges in adoption of the surgical prophylaxis prevention guidance. The baseline data collection will be done in this phase (pre-intervention data) on the baseline SSIs rates and practice followed in the setting. These findings will be helpful in co-development of the multipronged interventions during Phase-II.

### Phase-II (Co-development of a multipronged intervention package addressing the identified barriers and suitable for low resource settings by the stakeholders):

The multipronged interventions will be co-developed by the stakeholders based on the findings of scoping/literature review, baseline assessment, and available guidance. The stakeholders will involve the head of the departments of surgery, hospital administration (medical superintendent of the site), the investigators (PI and Co-PI) from respective sites involved. All the stakeholders will identify the practice gap in their setting from baseline data assessment. The most relevant, feasible and impactful interventions from observed clinical practices during baseline data collection phase, published guidance documents, scoping/literature review which are feasible as well as crucial in reducing the surgical site infections will be identified. [**Template example provided in Appendix-I**].

Series of discussions with all the stakeholders will be conducted to discuss the identified components of multipronged intervention. Any challenges foreseen in acceptability of the interventions will be discussed with the stakeholders before finalizing the components of the multipronged interventions. These interventions will then be mapped and all the stakeholders will reach on the consensus on which interventions to choose.

After finalizing the multipronged interventions among the stakeholders, the review will be done by the Project Advisory Group (PAG). The PAG will involve the senior academicians, external expert in the implementation research and PIs from the sites. The final multipronged interventions will be covering various core domains: system, structural and behavioral domains which will be implemented in the Phase-III as an intervention package.

After co-development, the standardization and monitoring plan of these multipronged interventions will be done as mentioned below (Figure 2)

**Figure 2: Development and standardization process of multipronged interventions**

**Intervention Standardization:** The steps of intervention standardization will include defining the type of standardization for each component and defining the limits of the standardization for each component^19^. The type and limits of the standardization will be set after consensus with the stakeholders and the project advisory group.

1. Type of standardization for each component and step can be classified into “mandatory” or “optional” or “prohibited”. “Mandatory” step must be performed under all circumstances and if not performed will be considered as protocol deviation; opposite is true for “Prohibited”. “Optional” step may or may not be performed at discretion of the participating surgeon.
2. Limits of standardization for each component can be set as “exactly” or “with boundaries” or “without boundaries (flexible)” based on the flexibility allowed for adoption by the health care professional. If mentioned as “with boundaries”, the component or step can be followed as per the amount of flexibility mentioned for each component of intervention. (Table -2)

**Intervention Monitoring:** The levels of fidelity will be defined and noted as per the levels mentioned in Table-1 after discussion with all the stakeholders. The discrepancy among the stakeholders will be resolved after discussion among each other for reaching to the final consensus. Based on the multipronged interventions, a checklist and standard data collection form will be developed. The check list developed will be used for assessing the level of fidelity and compliance to the multipronged interventions for each patient as shown is Appendix-I.

**Table-1**: Levels and type of intervention fidelity to be described for each component of the multipronged intervention^19^

| **Level of fidelity** | **Type and description** |
| --- | --- |
| Protocol deviation from intended intervention | Did not receive any intervention or received alternative intervention not being evaluated in the study |
| Deviation from component(s) of the intended intervention | Did not receive the component of the intervention or component of intervention delivered partially or component of intervention delivered in a different way than what is mentioned in the study protocol. |

The set of selected multipronged intervention package co-developed and standardized by all the stakeholders will be implemented among health care professionals.

**Outcome of Phase-II:** The expected outcome of Phase-II is to co-develop feasible and acceptable multipronged intervention package that can be implemented in the low-resource setting to prevent surgical site infections.

### Phase-III (Deployment of the multipronged interventions):

Phase-III will involve deployment of the multipronged interventions and process evaluation.

**Deployment of multipronged interventions:** Multipronged interventions developed in phase-II will be implemented in Phase-III using the following strategies: training of healthcare professionals, identification of Surgical site infection prevention (SSIP)/Stewardship champions, review of implementation by the project advisory committee.

**A. Structured training curriculum and training manual**: The structured training modules will be developed as per the multipronged interventions co-developed in Phase-II. The training modules will be contextualized to the practice change needs and the training sessions will be conducted using interactive sessions. The assessment will be applied pre and post-training among the health care professionals undergoing training to assess the practice and knowledge change adopted from the training modules. The assessment will also indicate the need for re-training.

**B. Training**: The project steering group (comprising of multidisciplinary team of PIs from the sites, antimicrobial stewardship experts) will impart comprehensive training of the relevant health care professionals including the operation theatre nursing staff involved in surgery and patient care, the residents, anesthesiologists’ and the surgeons using the structured training modules and curriculum using 4-5 interactive sessions, didactic lectures for adoption of the multimodal interventions spanned over a period of two months. The health care professions undergoing training will be assessed for practice and knowledge change using pre-developed assessment module. The score of >80% in the training assessment will be considered adequate. If score of <80%, then either re-training session will be conducted or not included in the study.

**C. Identification of SSIP/Stewardship Champions**: The “SSIP champions” will be identified for each setting by the site PI/Co-PI (could be ICN nurse/resident/surgeon who have leadership qualities and actively working in the surgery department). These SSIP champions will ensure the adoption of the multimodal interventions in their setting and will also assess the need of interim training or re-training in their respective sites. If the compliance to the multipronged interventions is not there at a particular site as assessed by the checklist of each patient, then re-training will be schedule. If non-compliance is persistent, then it will be communicated to the project advisory group. The process evaluation will be done by project advisory group and IDI will be conducted to understand the hurdles and challenges in adoption of these interventions and explained below.

**Process evaluation**: The compliance to the multipronged interventions as assessed by the SSIP champions will be evaluated by the project advisory committee. The SSIP champions will also evaluate whether the structural and system changes are in-place at respective sites and behavioural changes are adopted by the health care professionals. If there is non-compliance and is persistent, then the stakeholders will re-assess the acceptance of the co-developed multipronged interventions. In-depth interviews with the health care professionals will follow to understand the hurdles and challenges in accepting these interventions and troubleshooting iteratively. The multipronged interventions will be either adapted as per the challenges evolving or co-developed as per the site need or if only retraining will suffice, then re-training will be planned. The monitoring of the compliance to the multipronged interventions at each site using the checklist will be done by SSIP champions and reported to the project advisory group quarterly.

The intervention will continue with the help of SSI Champions and after the study is over also. The intervention and result assessment quarterly will go hand in hand and the impact assessment will follow.

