# STUDY ADMINISTRATION

## Data collection and management

Patients planned for general surgical procedures (elective or emergency) will be screened for inclusion in the study based on inclusion and exclusion criteria.

The data collection during baseline, post-intervention phase for the surgical patients undergoing elective or emergency surgery will be done by the Infection control nurse and research fellow in the standardized data collection form including but not limited to the data on timing of antimicrobial prophylaxis given, time of start of surgery, vitals, re-dosing of antimicrobial prophylaxis, time of stoppage of surgery, type of surgery (name of surgery; clean/clean-contaminated/contaminated/dirty), aseptic precautions taken or not, information on drains in situ, post-operative care, details of post-operative antimicrobials. The patient will be followed up regularly till discharge and data on SSI, antimicrobials, clinical outcome will be recorded. The patient will be called in-person for follow-up to ODP at 30-day to know the clinical status and outcome of the patient. Any unplanned visit to OPD or emergency will be noted with the reason of the visit.

If follow-up is not possible at 30 days after surgery, patients will be followed up as soon after this as possible or telephonically. If patient developed SSI before postoperative day 30, they will still be reviewed at 30 days after surgery to record secondary outcomes.

In intervention phase, in addition the checklist of multipronged interventions will be checked for implementation assurance along with the data collection form.

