# TOTAL BUDGET (TOTAL for all 7 centers)

| **S.NO** | **Particulars cumulative of all 7 centers** | **Year 1** | **Year 2** | **Year 3** | | **Total 3 years** |
| --- | --- | --- | --- | --- | --- | --- |
|  | **Staff/ Manpower** for the duration of | 10 months | 12 months | 10 months | | 32 months |
|  | 1. Project Technical Support-III (**5% increment in 3^rd^ year**)   @ 28,000 + 9% HRA = ~30,520 INR per month per centre (*4 centres)  @ 28,000 + 18% HRA = ~33,040 INR per month per centre (*3 centres) | 3,05,200 * 4 = 12,20,800 INR  3,30,400*3= 9,91,200 | 3,66,240*4= 14,64,960 INR  3,96,480*3= 11,89,440 | 3,20,460* 4 = 12,81,840 INR  3,46,920*3= 10,40,760 | | 71,89,000 INR |
|  | 1. Project staff Nurse (Project Nurse-II) (**5% increment in 3^rd^ year**)   @ 20,000 + 9% HRA = ~21,800 INR per month per centre (*4 centres)  @ 20,000 + 18% HRA = ~23,600 INR per month per centre (*3 centres) | 2,18,000 * 4 = 8,72,000 INR  2,36,000*3= 7,08,000 INR | 2,61,600*4 = 10,46,400 INR  2,83,200* 3= 8,49,600 INR | 2,28,900 * 4 = 9,15,600 INR  2,47,800*3= 7,43,400 INR | | 51,35,000 INR |
|  | Subtotal | 37,92,000 | 45,50,400 | 39,81,600 | | 1,23,24,000 INR |
|  | **Justification of Staff/Manpower:** Although each department has nursing staff, but the dedicated nurse is not provided by institute for antimicrobial stewardship work or project purpose. The project will need a dedicated nurse for the project to spare visit to the OT area posted and follow up of patients as the follow up is 30-days post-surgery (or 90-days if implant in situ) | | | | | |
|  | **Equipment Name** |  |  |  |  | |
|  | Desktop with Multifunctional Printer | 70,000 + 40,000 per Centre (*7) |  |  | 7,70,000 INR | |
|  | **Consumables (Recurring)** |  |  |  |  | |
|  | Printing and stationary | 50,000 per Centre (*7) |  |  | 3,50,000 INR | |
|  | **Contingency** |  |  |  |  | |
|  | Article Publication Charges (APC) for 2-3 manuscripts expected | 2,50,000 |  | 2,50,000 | 5,00,000 INR | |
|  | Miscellaneous | 2,00,000 |  |  | 2,00,000 INR | |
|  | **Travel and Meetings** |  |  |  |  | |
|  | Physical meeting of all PIs/Co-PIs: 5 (one before starting the study, three during study and one after study completion) visit to centre for training/data compilation and TA/DA to all collaborators | 1,00,000 | 3,00,000 | 1,00,000 | 5,00,000 INR | |

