|  | Use of alcohol chlorhexidine based pre-operative skin preparation if no contra-indication exists and aseptic precautions including hand hygiene. | Optional (Based on availability and patient factors, alcohol chlorhexidine based or Povidone iodine-based solution can be used for skin preparation with proper drying) | Flexible based on availability and surgeon choice |
|  | Controlled blood glucose during immediate post-operative period. | Optional | Boundaries (levels blood sugar to be mentioned as controlled varies as per patient characteristics) |
|  | Maintenance of perioperative normothermia (≥35.5°C) in surgical patients | Optional (maintained if duration of anesthesia >60 minutes) | Exactly (Patients where therapeutic hypothermia needed will be excluded from the study) |
|  | Minimizing the door opening of the operating room | Optional | Flexible |

**Table-3: Template Checklist to be checked for each patient based on the components of the multipronged interventions co-developed by the stakeholders.**

| S.NO | Interventions |  | Intervention followed or not (Yes or No) |
| --- | --- | --- | --- |
| 1 | Delivery of intravenous antimicrobial prophylaxis within 1 hour before incision (2 hr for vancomycin and fluoroquinolones) | Time of antimicrobial prophylaxis administration…………..  Time of start of surgery…………………. |  |
| 2 | Redosing of antimicrobial if interval >2 half-lives or if blood loss >1500 ml | Redosing required or not …….  Duration of surgery ………… |  |
| 3 | Use of antimicrobial prophylactic agent consistent with published guidelines | Name of antimicrobial given as surgical prophylaxis …………………………. |  |
| 4 | Discontinuation of prophylactic antimicrobial agent within 24 hours of surgery (within 48 hours for cardiothoracic procedures in adult patients) | Time of stoppage of surgery……………  Time and date of last dose of antimicrobial prophylaxis …………………………….. |  |
| 5 | Proper hair removal: No removal (if not hampering surgery) or use of clippers/depilator method. Use of razors to be considered inappropriate | Hair removed or not ………  If yes, method of hair removal …………………………… |  |
| 6 | Use of alcohol chlorhexidine based pre-operative skin preparation if no contra-indication exists and aseptic precautions including hand hygiene. | Agent used for skin preparation……………….. |  |
| 7 | Controlled blood glucose during immediate post-operative period. | Blood sugar levels 6 hourly in postoperative period …………  …………………………… |  |

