| 8 | Maintenance of perioperative normothermia (≥35.5°C) in surgical patients who have anesthesia >60 minutes | Temperature in intra-operative period ………….. |  |
| 9 | POD-1 review of antimicrobials. | Any advice given: ……………………………….  Advice followed or not? …………………………….. |  |
| 10 | SSI surveillance as per CDC/NHSN definition of SSI. | SSI surveillance done as per definition mentioned in Appendix-II …………….. |  |

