# Appendix-II: who SURGICAL SITE INFECTION SURVEILLANCE POST-OPERATIVE DATA COLLECTION FORM

# Appendix-IiI: DIAGNOSIS OF SURGICAL SITE INFECTION AS PER CDC

| **Superficial incisional SSI :** Must meet the following criteria:  Date of event occurs within 30 days following the operative procedure (where day 1 = the procedure date) **AND** involves only skin and subcutaneous tissue of the incision  **AND**  patient has at least ***one*** of the following:   1. purulent drainage from the superficial incision. 2. organism(s) identified from an aseptically-obtained specimen from the superficial incision or subcutaneous tissue by a culture or non- culture based microbiologic testing method which is performed for purposes of clinical diagnosis or treatment (for example, not Active Surveillance Culture/Testing [ASC/AST]). 3. a superficial incision that is deliberately opened by a surgeon, physician* or physician designee and culture or non-culture based testing of the superficial incision or subcutaneous tissue is not performed **AND** patient has at least one of the following signs or symptoms: localized pain or tenderness; localized swelling; erythema; or heat. 4. diagnosis of a superficial incisional SSI by a physician. |
| --- |
| **Deep incisional SSI**  Must meet the following criteria:  Date of event occurs within 30 or 90 days following the operative procedure (where day 1 = the procedure date) **AND** involves deep soft tissues of the incision (for example, fascial and muscle layers) **AND** patient has at least ***one*** of the following:   1. purulent drainage from the deep incision. 2. a deep incision that is deliberately opened or aspirated by a surgeon, physician or spontaneously dehisces   **AND**  organism(s) identified from the deep soft tissues of the incision by a culture or non-culture based microbiologic testing method which is performed for purposes of clinical diagnosis or treatment (for example, not Active Surveillance Culture/Testing [ASC/AST]) or culture or non- culture based microbiologic testing method is not performed. A culture or non-culture based test from the deep soft tissues of the incision that has a negative finding does not meet this criterion.  **AND**  patient has at least ***one*** of the following signs or symptoms: fever (>38°C); localized pain or tenderness.   1. an abscess or other evidence of infection involving the deep incision detected on gross anatomical exam, histopathologic exam, or imaging test. |

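### The protocol lets the infection control nurse who records SSI also serve as the site's SSIP champion, so the outcome recorder can gain a stake in the package in the second period only

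*Protocol*

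**What the plan says.** Who records SSI:
- Section 4.1 covers data collection in the baseline and post-intervention phases alike. It "will be done by the Infection control nurse and research fellow in the standardized data collection form", and SSI is among the data recorded up to discharge and at follow-up.
- Section 3.1.1 names much the same people for the first period: "The baseline data collection will be done by the trained research associate/ICN nurse for the patients undergoing surgeries".

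Who may be champion:
- Section 3.1.3, part C, says the champion "could be ICN nurse/resident/surgeon who have leadership qualities and actively working in the surgery department".
- The duty is explicit: "These SSIP champions will ensure the adoption of the multimodal interventions in their setting". Champions also judge the need for re-training, assess compliance and report it quarterly to the project advisory group.
- The role begins at deployment, so it does not exist in the baseline period.

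Safeguards already in the text:
- The post-intervention phase collects the same parameters on the CRF (section 3.1.4).
- The CDC definition applies to both periods (section 3.7).
- Section 6 justifies a funded nurse at each centre: "The project will need a dedicated nurse for the project to spare visit to the OT area posted and follow up of patients".

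Section 3.2, on allocation and blinding, is marked not applicable. No independent or masked adjudication of SSI is described.

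On the checklist, item 10 of Table-3 in Appendix-I reads "SSI surveillance as per CDC/NHSN definition of SSI". The table is titled "Template Checklist to be checked for each patient based on the components of the multipronged interventions co-developed by the stakeholders". Section 4.1 adds the checklist to the data form in the intervention phase only.

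**The concern.** The primary comparison is SSI before against SSI after, with no concurrent control. It is valid only if SSI is found and recorded in the same way in both periods. If the recording nurse becomes champion at deployment, the same person records as a neutral observer in the first period and, in the second, as someone answerable for the package's success. Some criteria leave room for judgement; in Appendix-III, "diagnosis of a superficial incisional SSI by a physician" is sufficient on its own for a superficial infection. A recorder with a stake might pursue or enter borderline cases less readily.

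Any such drift coincides exactly with the intervention period. Covariate adjustment, stratification by wound class and the planned Cox model cannot tell it from a real reduction. It has to be prevented by the assignment of roles, and that assignment is fixed in the protocol rather than being something an analysis plan would settle.

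**Working it through.** **Step 1. The roles side by side.**

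| Role | Baseline period | Intervention period | Source |
| --- | --- | --- | --- |
| Records SSI | Infection control nurse; research fellow or associate | Infection control nurse; research fellow | 3.1.1, 4.1 |
| SSIP champion | Role does not exist | Infection control nurse, resident or surgeon | 3.1.3 C |

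The infection control nurse can appear in both rows, and only in the second period. No sentence rules this out. The funded nurse in section 6 is not barred from being champion either.

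**Step 2. Reproduce the planned sizes.** Inputs from section 3.11: two-sided 5% level, 90% power, 15% loss; SSI 8% to 5% (clean), 12% to 8% (clean-contaminated), 30% to 20% (contaminated). With p̄ = (p1 + p2)/2, the number per period is

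n = [1.96·√(2p̄(1−p̄)) + 1.2816·√(p1(1−p1) + p2(1−p2))]² / (p1−p2)²

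This gives 1418 / 1181 / 392 evaluable per period. Multiplying by 1.15 gives 1631 / 1359 / 451; dividing by 0.85 gives 1669 / 1390 / 462. Both are within 3% of the stated 1630 / 1350 / 450. The sizes are not in dispute and serve only as the basis for the next step.

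**Step 3. Illustrate what a drift would do.** The protocol gives no drift figure, so the fraction m is an assumption. Suppose there is no true effect and the second period records a fraction m fewer SSIs overall, so that q = p1(1−m). Evaluable numbers are 85% of the stated sizes: 1385 / 1147 / 382 per period. With p̄ = (p1 + q)/2,

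P(significant reduction) = Φ{[(p1−q) − 1.96·√(2p̄(1−p̄)/n)] / √([p1(1−p1) + q(1−q)]/n)}

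Clean surgery, m = 0.20: q = 0.064, difference 0.016, both standard errors 0.0098. Then (0.016 − 1.96 × 0.00982)/0.00982 = −0.33, and Φ(−0.33) = 0.37.

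| Assumed m | Clean | Clean-contaminated | Contaminated |
| --- | --- | --- | --- |
| 0 (nominal) | 2.5% | 2.5% | 2.5% |
| 0.10 | 12% | 15% | 15% |
| 0.20 | 37% | 46% | 46% |
| 0.25 | 54% | 65% | 65% |

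**Step 4. Scale to partial overlap.** The table assumes a loss across all SSI at all sites. Suppose instead that the overlap arises at 3 of 7 equal-sized sites (assumed).
- Under-recording of 20% at those sites is 0.20 × 3/7 = 8.6% overall, which is below the 10% row.
- To reach 20% overall, those sites would have to lose 0.20/(3/7) = 47% of their SSIs.
- If only half of SSIs were borderline (assumed), that means losing 0.47/0.5 = 93% of the borderline ones.

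The 20% and 25% rows are therefore an upper range, not a central case.

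**The case against.** The strongest reply is that the protocol does not plan this overlap. The champion may be a resident or surgeon. A research fellow records alongside the nurse. A dedicated nurse is funded at every centre, and section 6 also pays for training of data collectors at the coordinating site. The same CRF and the same CDC definition apply throughout. All of that stands, and it makes the problem a possibility at some sites rather than a feature of the design. It does not close the gap: a common form and definition standardise the criteria but not the recorder's interest, and no sentence keeps recorder and champion apart.

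A second reply is that the judgement-based criteria are clinicians' decisions, and that surgeons and residents are trained in the package whether or not one of them is champion. This also stands. Separating the roles protects recording and case-finding but not diagnosis.

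Two stronger readings are tempting.
- **SSI surveillance is part of the intervention, so detection will rise after deployment and hide a benefit.** The documents do not support this. Table-3 is a template to be finalised in Phase II, Table-2 does not list surveillance among the components, and SSI is already collected on the CRF in both periods. A tick-box confirming that surveillance was done may or may not alter case-finding.
- **The trial carries a false-positive risk of 37-46%.** That figure follows only from an assumed 20% loss of all SSI, which nothing in the protocol supports.

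**Conclusion.** The point holds in limited form. Sections 3.1.3 and 4.1 together allow the person recording the primary outcome to take on responsibility for the package between the two periods compared. In an uncontrolled before-after design, any resulting drift in recording cannot be separated from the effect. The overlap is permitted, not mandated, and whether it occurs depends on each site's choice of champion.

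The size is unknown. The illustration (12-15% at an assumed 10% overall drift, 37-46% at 20%, against 2.5%) rests on no true effect, the stated sizes less 15% loss, and a uniform loss across sites and SSI types. Partial overlap gives less. The case for acting is that the change is cheap and the bias cannot be repaired afterwards; it is not that a large bias has been shown.

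Item 10 of Table-3 is a secondary point that depends on what Phase II retains.

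**What to change.** 1. State in sections 3.1.3 and 4.1 that nobody who records SSI for the study may be an SSIP champion.
2. State in section 4.1 that the same funded project staff at each centre (the project nurse and the technical support person in section 6) record SSI in both periods.
3. When the checklist is finalised in Phase II, leave out item 10 and keep SSI surveillance on the CRF used in both periods.
4. State as a limitation that clinicians who know the period, and are trained in the package, diagnose superficial SSI. The changes above do not remove that bias.

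The cost is protocol wording; the staff are already budgeted. The one practical drawback is that a site must choose a champion other than its data-collecting nurse.
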